## Abstract

**Introduction::**

Stroke is the leading cause of disability-adjusted life years in neurological diseases and has become one of the top 3 fatal diseases in the world. Cerebral hemorrhage accounts for approximately 18% to 24% of all strokes in Asian countries. Cerebral hemorrhage is one of the most destructive subtypes of stroke and has high morbidity and mortality. Based on the current research, it has been confirmed that neither surgical treatment nor current drug treatment is the most preferred treatment. Traditional Chinese medicine (TCM) is increasingly being used to treat cerebral hemorrhage, and the activating blood and removing stasis (ABRS) method has received more attention. At present, there is still a lack of high-quality clinical research on the treatment of acute cerebral hemorrhage.

**Method::**

We designed a multicenter, prospective, randomized, double-blind, placebo-controlled clinical trial. We aim to recruit 312 cerebral hemorrhage patients aged 18 to 80 years within 24 to 72 hours after onset. In addition to routine treatment, participants will randomly receive ABRS granules or placebo for 14 days. Those enrolled within 24 to 48 hours after onset will enter strata A, and those enrolled within 49 to 72 hours (including 48–49 hours) after onset will enter strata B. The strata sample size ratio will be 1:1. The primary outcome is the disability degree (modified Rankin Scale score, mRS) at 6 months after onset. The secondary outcomes include the percentage of hematoma enlargement after treatment, Barthel index (BI), National Institutes of Health stroke scale (NIHSS) score, mortality rate, all-cause mortality rate, TCM stroke syndrome evaluation scale score, and adverse events.

**Discussion::**

The study is expected to confirm the safety and effect of acute cerebral hemorrhage within 24 to 72 hours treated with the ABRS method and to determine the optimal time for intervention in this period.

**Trial registration number::**

ChiCTR1900022627

## Introduction

1

Stroke is the leading cause of disability-adjusted life years in neurological diseases and has become one of the top 3 fatal diseases in the world.^[1]^ Cerebral hemorrhage accounts for approximately 18% to 24% of all strokes in Asian countries, which is higher than that in Western countries.^[2]^ Cerebral hemorrhage is one of the most destructive subtypes of stroke and has high morbidity and mortality.^[3]^ The median mortality rate within 1 month was 40.4%, and the functional dependence after cerebral hemorrhage was approximately 75%.^[4]^ At the same time, it was found that hematoma enlargement was closely related to prognosis.^[5,6]^ Approximately one-third of patients with cerebral hemorrhage have hematoma growth within 24 hours.^[7,8]^ However, there is no specific treatment to prevent hematoma enlargement and promote hematoma absorption to improve the prognosis. In addition, based on the current research, it has been confirmed that neither surgical treatment nor current drug treatment is the most preferred treatment.^[9,10]^

In the face of the limitations of the treatment for cerebral hemorrhage, traditional Chinese medicine (TCM) is increasingly used to treat cerebral hemorrhage.^[11,12]^ According to the theory of traditional Chinese medicine, “abnormal flow of the blood is stasis,” so stasis occurs throughout the pathological process of cerebral hemorrhage. Therefore, the key to the treatment of cerebral hemorrhage is activating blood and removing stasis. At present, there are studies focusing on the therapeutic effect of activating blood and removing stasis, but there is still a lack of high-quality clinical research on the treatment of acute cerebral hemorrhage.

We designed a multicenter, prospective, randomized, double-blind, parallel controlled clinical trial to evaluate the optimal intervention time, efficacy and safety of the activating blood, and removing stasis method for acute cerebral hemorrhage within 24 to 72 hours after onset.

## Methods and design

2

### Study design and setting

2.1

The study is a multicenter, prospective, randomized, double-blind, placebo-controlled clinical trial. Participants will be randomly assigned to the activating blood and removing stasis (ABRS) granule group or placebo group. Group allocation ratio is 1:1. The patients were stratified according to the time of enrollment. Patients who enrol within 24 to 48 hours after onset will enter strata A, and patients who enrol within 49 to 72 hours (including 48–49 hours) after onset will enter strata B. The strata sample size ratio is 1:1. Participants will receive ABRS granules in addition to routine treatment or placebo in addition to routine treatment. The treatment cycle is 14 days. The primary outcome is disability degree (modified Rankin scale score). This study is reported in accordance with the Standard Protocol Items: Recommendations for Interventional Trial (SPIRIT) guidelines.^[13]^ The study flow chart is shown in Fig. 1.

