#### Exclusion criteria

2.3.2

1.Cerebral hemorrhage was confirmed to be caused by a brain tumor, blood disease, or brain trauma (or postoperative).2.Coma or cerebral hernia at the onset of cerebral hemorrhage.3.Inability to take the study drug orally or nasally because of gastrointestinal bleeding.4.Emergency surgery.5.Subarachnoid hemorrhage.6.Pregnancy or lactation.7.Severe primary disease, such as cardiovascular, hepatic, renal and hematopoietic disease, mental disease, or abnormal (double the normal level) results on routine coagulation, liver function, and kidney function evaluations.8.Allergic constitution or known allergy to alcohol or ingredients of TCM ABRS granules.9.Hemorrhagic stroke induced by anticoagulant drugs.10.Participation in other clinical trials in the last 3 months.

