### Recruitment

2.4

Inpatients with cerebral hemorrhage in all recruiting centers will undergo screening assessments to determine their eligibility. Patients meeting all of the inclusion criteria and none of the exclusion criteria will be informed of this study. All participants will be fully informed of the purpose, process, other treatment options, risk and benefit of the study, and sign an informed consent form if they agree to participate.

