### Randomization and treatment allocation

2.5

Randomization will be performed immediately after signed informed consent has been obtained. This study will use a stratified block randomization design, with stratification by recruiting center and time of enrollment. Randomization will be performed by the Center for Evidence-Based Chinese Medicine of Beijing University of Chinese Medicine using SAS version 9.2 (Cary, NC). Participants will be randomized at a 1:1 ratio to the ABRS granule group or the placebo group.

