The results of this study will be of importance for patients with cerebral hemorrhage, as they will allow us to draw conclusions on the efficacy, safety, and optimal timing of intervention with the ABRS method. This study may provide clinical evidence as a basis for the treatment of acute cerebral hemorrhage with the ABRS method and improve the prognosis and quality of life of patients with cerebral hemorrhage.

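### Start time is not randomized, so a difference between the two enrollment-time strata cannot identify an optimal intervention time

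*Protocol article*

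**What the plan says.** **How a stratum is assigned.** Section 2.1 of the protocol article: "The patients were stratified according to the time of enrollment". Stratum A is 24 to 48 h after onset; stratum B runs from there to 72 h. The same section adds: "The strata sample size ratio is 1:1".

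**What is randomized.** Section 2.5: "Participants will be randomized at a 1:1 ratio to the ABRS granule group or the placebo group". Time enters only as a stratification factor, "with stratification by recruiting center and time of enrollment".

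**What sets the hour of treatment.** Section 2.5: "Randomization will be performed immediately after signed informed consent has been obtained". Under section 2.7 study treatment follows randomization at once, so the hour of enrollment is the hour of start.

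**Who can enroll.** Section 2.4: "Inpatients with cerebral hemorrhage in all recruiting centers will undergo screening assessments to determine their eligibility". Section 2.3.1 requires conservative treatment and a Glasgow score above 6. Section 2.3.2 excludes "Emergency surgery".

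**What is promised.** Section 2.2 makes determining the best intervention time part of the objective, and the abstract's Discussion says the same. Of the results, the closing paragraph of section 3 says that "they will allow us to draw conclusions on the efficacy, safety, and optimal timing of intervention with the ABRS method". The only limitation named in section 3 is that the trial runs in China alone.

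**The concern.** A claim about the best time to start is a causal claim: the same patients would do better if started in one window than in the other. That needs either random assignment of start time or an argument that patients in the two windows are alike. The protocol has neither.

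The two windows also filter patients differently. Taking the eligibility criteria to apply at enrollment, anyone entering B must still meet them after 48 h, while patients lost in the preceding 24 h could have been counted in A. If those patients differ in severity or hematoma volume, and the benefit of ABRS depends on such features, the treatment effect will differ between strata even when start time has no influence.

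What is at stake is a stated objective. A difference produced by case mix could be published as a recommendation on when to treat. Neither a larger sample nor a correctly specified test would cure this, because the problem lies in how patients reach a stratum.

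**Working it through.** **1. The plan's own figure.** Section 2.12 gives 56% versus 36% unfavorable, a two-sided Z test, and 129 per group. Alpha is 0.05 (section 2.13); power is not stated, so 90% is assumed. With a pooled variance and mean rate 0.46:

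n = [1.960·√(2·0.46·0.54) + 1.282·√(0.56·0.44 + 0.36·0.64)]² / 0.20²
= (1.381 + 0.885)² / 0.04 ≈ 128.4, rounded up to 129.

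The figure reproduces. It sizes the overall ABRS-placebo comparison, not a comparison of strata. An even split of 312 gives 156 per stratum and 78 per arm within a stratum.

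**2. Selection between the windows.** The protocol gives no rates of death, surgery or deterioration between 24 and 72 h. Section 1 cites 40.4% mortality at one month, which cannot be apportioned to this interval. So assume that a share y of patients eligible at 24 to 48 h can no longer enter B, that all of them would have an unfavorable outcome in either arm, and that start time has no effect. Then:

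- Stratum A: placebo 56%, ABRS 36%, difference 20 points.
- Stratum B: placebo (0.56 − y)/(1 − y), ABRS (0.36 − y)/(1 − y), difference 0.20/(1 − y).

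| y (assumed) | Placebo in B | ABRS in B | ABRS-placebo difference in B | Excess over A | Treated patients only, A minus B |
|---|---|---|---|---|---|
| 5% | 53.7% | 32.6% | 21.1 | 1.1 | 3.4 |
| 10% | 51.1% | 28.9% | 22.2 | 2.2 | 7.1 |
| 15% | 48.2% | 24.7% | 23.5 | 3.5 | 11.3 |

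The fifth column applies to the difference between strata in the randomized contrast. The last applies only if treated patients in A and B were compared directly, ignoring the placebo arms.

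**3. Effect modification.** Suppose instead that benefit is 30 points in milder and 10 points in severer patients (assumed), again with no timing effect.

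- 60% severe in A, 40% in B: A = 0.4·30 + 0.6·10 = 18; B = 0.6·30 + 0.4·10 = 22; gap 4 points.
- 70% severe in A, 30% in B: A = 0.3·30 + 0.7·10 = 16; B = 0.7·30 + 0.3·10 = 24; gap 8 points.

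**4. Precision of the between-stratum contrast.** With a true 20-point effect in both strata, the standard error is √[2·(0.56·0.44 + 0.36·0.64)/n].

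- n = 78 per arm per stratum: √(0.9536/78) = 0.111, 95% half-width about 22 points.
- n = 62 (78·0.8, after 20% loss): √(0.9536/62) = 0.124, half-width about 24 points.

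**The case against.** The strongest reply is that each stratum has its own concurrent randomized placebo group, and section 2.13 confines comparisons to ABRS versus placebo. A better natural course in B, or a drift over calendar time, then affects both arms alike and largely cancels. This stands. It is why the 3 to 11 point figure, which a reader might take as the bias in the timing result, does not apply to the planned comparison; under the same assumptions the spurious gap is 1.1 to 3.5 points. That is also small beside a half-width of 22 to 24 points. But the cancellation covers prognosis only. It does not cover features that change the size of the treatment effect, and any statement on optimal time needs the comparison across strata.

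A reader might also infer that the 1:1 ratio is a quota that closes one stratum, with sites then holding inpatients past 48 h to fill the other. The protocol does not say this. It fixes the ratio, not how the ratio is reached. Deferral is possible because nothing in the text rules it out, but it is not described, and the argument does not depend on it.

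Third, section 2.13 promises adjustment for baseline imbalances and a later statistical plan. The choice of covariates can fairly be left to that plan. However, the adjustment is stated for a comparison of ABRS with placebo, and no analysis plan can make an observed enrollment hour a randomized one.

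**Conclusion.** The point holds as a mismatch between design and claim. The trial can estimate the ABRS-placebo effect in patients enrolled early and in patients enrolled late, each without bias from this source. It cannot attribute a difference between those effects to start time, so the optimal-time statements in the abstract, section 2.2 and section 3 go beyond the design. The overall ABRS-placebo comparison is not affected.

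The size of the bias is unknown. The 1.1 to 3.5 points rest on an assumed loss of 5% to 15% with uniformly unfavorable outcomes. The 4 to 8 points rest on assumed severity mixes and assumed effects. These figures show that a spurious gap can arise; they do not estimate it. Nor does the text establish that stratum B has the better prognosis. It shows only that entry to B is conditional on events that entry to A is not.

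**What to change.** 1. In the abstract's Discussion, section 2.2 and the closing paragraph of section 3, restate the timing aim as whether the ABRS-placebo effect differs between patients enrolled at 24 to 48 h and at 48 to 72 h. Test this by a treatment-by-stratum interaction adjusted for baseline NIHSS and hematoma volume on the enrollment CT. Table 1 already schedules both assessments at enrollment.
2. State in the same places that enrollment time is not randomized and that no optimal start time will be claimed.
3. Add to section 2.4 that eligible inpatients are offered enrollment at the first eligible time and are not deferred to fill stratum B. This removes discretion over the stratum; it does not make the strata exchangeable. It has to be set during recruitment, because later analysis cannot recover it.

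The 1:1 ratio need not be dropped: equal strata help the precision of the interaction. Enrollment and onset times need no new rule, since assigning a stratum already requires them.

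The cost is reworded objectives and one recruitment rule, with no extra patients. The downside is a more modest timing conclusion and possibly slower balancing of the strata.

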**Figure 1 F1:**
[figure not shown]
Study design diagram. BI = Barthel index, mRS = modified Rankin scale, NIHSS = National Institutes of Health stroke scale, TCM = traditional Chinese medicine, TCM = traditional Chinese medicine.

We will conduct this study in 7 hospitals in China. These hospitals are The First Hospital of Jilin University, The Second Hospital of Jilin University, China-Japan Union Hospital of Jilin University, Dongfang Hospital Beijing University of Chinese Medicine, Jilin Province People's Hospital, Jilin Hospital of Integrated Traditional Chinese and Western Medicine in Jilin Province, and Liaoyuan Traditional Chinese Medicine Hospital.

### Study objectives

2.2

The objective is to investigate the efficacy and safety of the ABRS method for acute cerebral hemorrhage and to determine the optimal intervention time.

### Eligibility criteria

2.3

#### Inclusion criteria

2.3.1

1.Diagnosis with cerebral hemorrhagic stroke confirmed by computed tomography (CT).2.Age between 35 and 80 years old.3.Stroke onset time within 24 to 72 hours.4.Receive conservative medical treatment.5.Glasgow coma score >6 points.6.mRS score before onset of 0 to 1 point.7.Informed consented.

#### Exclusion criteria

2.3.2

1.Cerebral hemorrhage was confirmed to be caused by a brain tumor, blood disease, or brain trauma (or postoperative).2.Coma or cerebral hernia at the onset of cerebral hemorrhage.3.Inability to take the study drug orally or nasally because of gastrointestinal bleeding.4.Emergency surgery.5.Subarachnoid hemorrhage.6.Pregnancy or lactation.7.Severe primary disease, such as cardiovascular, hepatic, renal and hematopoietic disease, mental disease, or abnormal (double the normal level) results on routine coagulation, liver function, and kidney function evaluations.8.Allergic constitution or known allergy to alcohol or ingredients of TCM ABRS granules.9.Hemorrhagic stroke induced by anticoagulant drugs.10.Participation in other clinical trials in the last 3 months.

### Recruitment

2.4

Inpatients with cerebral hemorrhage in all recruiting centers will undergo screening assessments to determine their eligibility. Patients meeting all of the inclusion criteria and none of the exclusion criteria will be informed of this study. All participants will be fully informed of the purpose, process, other treatment options, risk and benefit of the study, and sign an informed consent form if they agree to participate.

### Randomization and treatment allocation

2.5

Randomization will be performed immediately after signed informed consent has been obtained. This study will use a stratified block randomization design, with stratification by recruiting center and time of enrollment. Randomization will be performed by the Center for Evidence-Based Chinese Medicine of Beijing University of Chinese Medicine using SAS version 9.2 (Cary, NC). Participants will be randomized at a 1:1 ratio to the ABRS granule group or the placebo group.

### Blinding

2.6

The study will be a double-blinded clinical trial. All personnel, researchers, care providers, and participants will remain blinded to the intervention being received. The placebo is identical in appearance, smell, and packaging to the ABRS granules. The indications for deblinding are serious adverse events (SAEs) as instructed by the local medical ethical review committee or other dire emergencies. We set up emergency code-breaking envelopes for deblinding for individual participants.

### Intervention

2.7

In addition to routine treatment (including general treatment, control of blood pressure, reduced intracranial pressure, and so on) according to the guidelines, participants will immediately receive ABRS granules or placebo after randomization. The preferred method of intervention will be oral; if the patient cannot swallow normally, the drug will be given nasally. The dosage will be 1 packet (15 g) twice a day for 14 days. The ABRS granule or placebo will be completely dissolved in 150 mL of boiling water before administration. The ABRS granule contains 8 kinds of herbs. The placebo was made from 5% ABRS granule and dextrin. The ABRS granules and placebo were produced and packed by China Resources Sanjiu Medical and Pharmaceutical Co., Ltd., Shenzhen, China, and passed the quality inspection before leaving the factory. The researchers have completed unified training and will patiently communicate with participants to increase compliance. Participants with <80% medication compliance will be excluded.

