#### Primary outcome

2.9.1

The primary outcome will be the disability degree (mRS score) at 6 months after onset. The mRS is widely used to assess disability in stroke patients.^[14]^ The mRS divides the disability degree into 6 grades, and the score ranges from 0 to 5. A higher mRS score indicates a more serious degree of disability.

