### Safety assessment

2.10

Safety will be evaluated according to the incidence of adverse events and the results of clinical laboratory examinations. All adverse events will be recorded. The possible association between adverse events and the intervention will be determined according to a 5-level classification: affirmative, probable, possible, suspicious, and impossible.

Any adverse events during the trial will be recorded using the “adverse event form” and continue to be investigated. Researchers will record the treatment process if needed and results until the laboratory examination results return to normal and symptoms and signs disappear. All SAEs will be reported to the research ethics committee within 24 hours. When participants become unsuitable to continue the trial due to adverse events, they will be withdrawn from the trial immediately.

Clinical laboratory examinations will include routine blood, urine, stool + occult blood, liver function, kidney function, coagulation function, glucose and D-dimer tests, and electrocardiography.

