### Statistical analysis

2.13

Inferential statistical analyses as specified will be conducted, and all comparisons will be between the ABRS granule group and the placebo group. The statistical analyst will be blinded to the participants’ personal information and group assignment during the trial. The primary analysis will be based on the full dataset following the intention-to-treat analysis principle for all efficacy outcomes, while the secondary analysis will be based on the per protocol dataset. For the analysis of safety outcomes, a safety dataset will be used. The primary outcome will be determined by a comparison of the changes in the patients’ mRS scores between the 2 groups at 6 months after onset. The secondary outcomes will include the mortality rate, hematoma enlargement percentage, all-cause mortality rate, adverse events, TCM stroke syndrome evaluation scale score, BI, and NIHSS score. The hematoma enlargement percentage will be measured at baseline, 24, 48, and 72 hours after taking the medicine and 14 days after onset. The mortality rate, all-cause mortality rate, BI, and TCM stroke syndrome evaluation scale score will be measured at 14 days, 3 months, and 6 months after onset. The NIHSS score will be measured at 14 days after onset. The mRS score will be measured at 3 and 6 months after onset.

Missing data regarding the primary and secondary outcomes will be imputed using the last observation carried forward (LOCF) method. Independent *t* tests or Wilcoxon rank-sum tests will be used to analyze continuous outcomes. Chi-squared tests will be used to analyze categorical data. Analysis of variance or a generalized linear mixed model will be used for repeated measurement data. Regarding mortality, survival probabilities will be estimated using the Kaplan–Meier method. Two-sided 95% confidence intervals will be constructed for assessment, and a 2-sided alpha level of 0.05 will be used to indicate significance. Adjustments will be made for baseline imbalances. Descriptive statistics, including the number and percentage for categorical variables and the number, mean, standard deviation, median, minimum and maximum for continuous variables, will be provided. Listings of individual patient data will also be produced. A comprehensive statistical plan will be prepared and finalized prior to unblinding and analysis of the data.

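### The 80% compliance exclusion in section 2.7 names no analysis set and, read literally, conflicts with the intention-to-treat primary analysis in section 2.13

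*Protocol article*

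**What the plan says.** All references are to the protocol article.

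- Section 2.7 (Intervention), after the dosing description: "Participants with <80% medication compliance will be excluded". It names no analysis set and does not say how compliance is computed.
- Section 2.13 (Statistical analysis): "The primary analysis will be based on the full dataset following the intention-to-treat analysis principle for all efficacy outcomes". A per-protocol set, not defined further, serves for a second analysis. On harms, the section adds: "For the analysis of safety outcomes, a safety dataset will be used".
- Section 2.10 (Safety assessment): "When participants become unsuitable to continue the trial due to adverse events, they will be withdrawn from the trial immediately". The object of the withdrawal is the trial, not the study drug.
- Section 2.13 on missing values: "Missing data regarding the primary and secondary outcomes will be imputed using the last observation carried forward (LOCF) method".
- Section 2.13 on timing: "The mRS score will be measured at 3 and 6 months after onset". Table 1 adds one mRS at enrollment and none in between.
- Section 2.9.1 (Primary outcome): "The mRS divides the disability degree into 6 grades, and the score ranges from 0 to 5". The scale as described has no grade for death.

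**The concern.** An intention-to-treat analysis keeps every randomized patient in the arm to which he or she was assigned. A rule that drops patients for something that happens after randomization undoes that. Sections 2.7 and 2.13, each taken at its word, give different answers for the same patient: one with 70% compliance is out under the first and in under the second.

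The dropped patients would probably not be a random sample. In acute cerebral hemorrhage, death and early deterioration are among the reasons for an incomplete 14-day course. If these losses differ by arm, the groups left for comparison differ in prognosis. The arm that loses more poor-outcome patients then looks better than it is.

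Section 2.10 raises a related but separate question: whether a patient taken out because of an adverse event still has a 6-month mRS measured. If not, the primary outcome for that patient is a carried-forward value.

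**Working it through.** **1. The plan's own figure.** Inputs from section 2.12: 56% unfavorable on control, 36% on treatment, two-sided Z test, 129 per group. Alpha is 0.05 (section 2.13). Power is not stated; 90% is assumed because it reproduces the figure. With mean proportion 0.46:

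n = [1.960 × √(2 × 0.46 × 0.54) + 1.2816 × √(0.56 × 0.44 + 0.36 × 0.64)]² / 0.20² = (1.381 + 0.885)² / 0.04 ≈ 128.4, so **129 per group**.

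This matches. The 56% is used below as the unfavorable rate, and 312 / 2 = 156 as the number per arm. The point at issue is bias and does not depend on the sample size.

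**2. Whom the 80% rule catches.** Section 2.7 gives two packets a day for 14 days: 2 × 14 = 28 packets, and 0.80 × 28 = 22.4.

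- 22 packets (11 full days): 22/28 = 78.6%, below the cut-off.
- 23 packets: 23/28 = 82.1%, above it.

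So *if* compliance is counted against the 28 planned packets, a patient who dies or stops before the 23rd packet falls under the rule. That denominator is an assumption. If compliance were counted against packets due up to the day of death or stopping, a patient who took every packet until then would score 100% and would not be caught.

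**3. What unequal exclusion would do.** Assumptions, none of them from the article: no true effect, a 56% unfavorable rate in both arms, every excluded patient unfavorable, and the exclusion fractions shown. With fraction e excluded, the observed rate is (0.56 − e) / (1 − e).

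| Excluded, placebo / ABRS | Placebo rate | ABRS rate | Apparent ABRS benefit | Chance of significance favoring ABRS |
|---|---|---|---|---|
| 5% / 5% | 0.51/0.95 = 53.7% | 53.7% | 0 | 2.5% |
| 5% / 10% | 53.7% | 0.46/0.90 = 51.1% | 2.6 points | 6.4% |
| 5% / 15% | 53.7% | 0.41/0.85 = 48.2% | 5.4 points | 14.7% |
| 10% / 5% | 51.1% | 53.7% | −2.6 points | not computed |

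The last column uses a pooled two-sample Z test on the patients left from 156 per arm. For 5% / 10%, that is 148.2 and 140.4 patients, a pooled rate of 0.524 and a standard error of 0.0588. Then z = 0.0257/0.0588 = 0.44, and Φ(0.44 − 1.96) = 6.4%. The nominal value is 2.5%.

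The illustration uses the unfavorable/favorable split of section 2.12. Section 2.13 compares changes in mRS score, so the points do not transfer directly to that scale.

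**4. The withdrawal sentence.** mRS is taken at enrollment, 3 months and 6 months. A patient withdrawn during the 14-day course and not seen again has only the enrollment value, and LOCF makes it the 6-month value. If change is measured from enrollment, it is then exactly zero. The direction of any bias is uncertain.

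**The case against.** The best defense is that section 2.13 governs the analysis and already separates intention-to-treat, per-protocol and safety populations. An 80% cut-off is a natural per-protocol criterion, and on that reading both sections can be followed. The article also promises a full statistical plan before unblinding, where set definitions usually sit. This defense stands in part: the per-protocol reading is plausible, and removal from the primary analysis is not proven. It does not dispose of the point. The rule as printed is unqualified and stands in the section that sites work from, and excluded could equally mean no further visits. A later analysis plan cannot recover outcomes that were never collected.

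A reader might also infer several stronger claims that the documents do not support.

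- *That early deaths are removed from the primary analysis.* This needs both the literal reading and the 28-packet denominator, and neither is confirmed.
- *That everyone with an adverse event is withdrawn.* Section 2.10 covers only those whom an adverse event makes unfit to carry on.
- *That withdrawal contradicts intention-to-treat.* A patient whose outcome is imputed by LOCF is still in the analysis. Section 2.10 also does not say that outcome visits stop, and it has adverse events followed until they resolve.
- *That harm would be hidden.* Safety has its own dataset, and mortality is a separate outcome at 14 days, 3 months and 6 months with Kaplan–Meier estimates. Nothing applies the 80% rule there.
- *That the bias favors ABRS.* No exclusion rates by arm are given. Equal exclusion under the assumptions above gives none, and the reverse imbalance works against ABRS. Even the 5.4-point case is about a quarter of the planned 20 points.

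**Conclusion.** The concern holds in limited form. Sections 2.7 and 2.13 conflict as worded and must be reconciled, because the first states without limit a post-randomization exclusion that the primary analysis in the second rules out. This is a stated rule that would give a wrong result if followed, not a detail left to another document.

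Its size cannot be fixed from the article. It is zero if the rule was meant for the per-protocol set or, under the assumptions above, if both arms lose equally. It is 2.6 to 5.4 points in the unequal examples, toward whichever arm loses more poor-outcome patients. Those figures rest on assumed exclusion rates and on every excluded patient being unfavorable, which is an extreme case.

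The withdrawal sentence in section 2.10 is a smaller, separate weakness. It is compatible with intention-to-treat, but if follow-up ends, an enrollment score stands in for the 6-month primary outcome.

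**What to change.** - **Section 2.7:** state that compliance below 80% removes a participant from the per-protocol set only, and that the primary analysis includes all randomized participants in their assigned arm. State the compliance denominator in the same place.
- **Section 2.10:** state that stopping study drug does not end the 3- and 6-month mRS, Barthel index and mortality assessments already in Table 1, unless the participant withdraws consent.

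The clinical criteria for stopping study drug are not touched. The cost is a few sentences plus follow-up contact with patients who are off study drug. No new visit or measurement is needed. Table 1 records adverse events only at enrollment and 14 days, and this change does not extend that.
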